# Effects of Pycnogenol® in people with post-COVID-19 condition (PYCNOVID): study protocol for a single-center, placebo controlled, quadruple-blind, randomized trial

**DOI:** 10.1186/s13063-024-08187-6

**Published:** 2024-06-15

**Keywords:** COVID-19, Post-COVID-19 condition, Pycnogenol®, Long COVID, SARS-CoV-2, Coronavirus

## Abstract

**Background:**

A significant proportion of the global population has been infected with severe acute respiratory syndrome coronavirus 2 (SARS-CoV-2) at some point since the onset of the pandemic. Although most individuals who develop coronavirus disease 2019 (COVID-19) recover without complications, about 6% have persistent symptoms, referred to as post-COVID-19 condition (PCC). Intervention studies investigating treatments that potentially alleviate PCC-related symptoms and thus aim to mitigate the global public health burden and healthcare costs linked to PCC are desperately needed. The PYCNOVID trial investigates the effects of Pycnogenol®, a French maritime pine bark extract with anti-inflammatory and antioxidative properties, versus placebo on patient-reported health status in people with PCC.

**Methods:**

This is a single-center, placebo-controlled, quadruple blind, randomized trial. We aim to randomly assign 150 individuals with PCC (1:1 ratio) to receive either 200 mg Pycnogenol® or placebo daily for 12 weeks. Randomization is stratified for duration of PCC symptoms (≤ 6 months versus > 6 months) and presence of symptomatic chronic disease(s). The primary endpoint is perceived health status at 12 weeks (EuroQol—Visual Analogue Scale) adjusted for baseline values and stratification factors. Secondary endpoints include change in self-reported PCC symptoms, health-related quality of life, symptoms of depression and anxiety, cognitive function, functional exercise capacity, physical activity measured with accelerometry, and blood biomarkers for endothelial health, inflammation, coagulation, platelet function, and oxidative stress. Investigators, study participants, outcome assessors, and data analysts are blinded regarding the intervention assignment. Individuals with PCC were involved in the design of this study.

**Discussion:**

This is the first trial to investigate the effects of Pycnogenol® versus placebo on patient-reported health status in people with PCC. Should the trial proof clinical effectiveness, Pycnogenol® may serve as a therapeutic approach to mitigate symptoms associated with PCC.

**Trial registration:**

The study is registered at ClinicalTrials.gov. :NCT05890534, June 6, 2023.

## Introduction

### Background and rationale {6a}

The coronavirus disease (COVID-19) pandemic has resulted in an ever-growing population of individuals recovering from a severe acute respiratory syndrome coronavirus 2 (SARS-CoV-2) infection. While most exhibit uncomplicated recoveries, a significant number experiences significant sequelae long after the acute illness has passed [1–7]. Population-based studies looking into PCC report a prevalence of about 20% of individuals with confirmed infection and about 6% of all infected with SARS-CoV-2 [8, 9]. While prolonged and persistent symptoms are more common among individuals who required hospitalization or experienced medical complications during the acute infection, data suggests that even some of those who experienced mild to moderate acute disease report persistent symptoms [2, 10]. Data from our population-based cohort study (Zurich SARS-CoV-2 Cohort) provide a comprehensive assessment of symptoms and information on the natural course of PCC [1, 3, 11]. In this cohort study, about 70% had mild symptoms, 20% had moderate symptoms, and 10% had severe symptoms and reported reduction in health status. Although symptom burden and severity of symptoms improved over time, about 18% of individuals with confirmed infection who were not vaccinated at the time of infection report persisting symptoms up to 2-years after infection [1].

With the increasing number of individuals affected from PCC there is also a growing effort from the scientific community to find effective therapeutic options [12]. Several countries have established a research agenda to prioritize research on PCC. Current research focuses on therapies to improve symptoms and functional status but also to understand pathomechanisms underlying post-COVID-19 sequelae (e.g., inflammatory processes, endothelial dysfunction) [13–16]. While the underlying pathophysiology of PCC remains unclear, some potential mechanisms include virus-specific pathophysiologic changes, ongoing immune stimulation from viral reservoirs in various tissues, persistent endotheliopathy, autoimmunity, hypercoagulation, and microthrombi as a result of an excessive inflammatory response [13, 14, 17].

It is important to find treatments with a favorable balance of benefits and harms. While a number of treatments under investigation may have considerable harms [12, 18, 19], Pycnogenol® may be an attractive treatment option since it is on the market for a long time with few side effects reported to date [20, 21] and some promising results in patients with PCC [20]. Pycnogenol® is a French maritime pine bark extract and primarily consists of procyanidins and their individual components, namely catechin and epicatechin, alongside phenolic acids [22]. It exerts antioxidative, anti-inflammatory, and antiproliferative properties and has been shown to improve vascular endothelial function, most likely due to an upregulation of endothelial nitric oxide synthase activity [21–25]. In people recovering from COVID-19, daily intake of 150 mg Pycnogenol® over a period of 12 weeks improved endothelial function and inflammatory and antioxidative biomarkers compared to control (usual treatment) [20]. Considering the potential beneficial effects of Pycnogenol® on disease characteristics of COVID-19 and PCC, it may improve the health status and alleviate symptoms in people with PCC.

### Objectives {7}

The primary objective of this randomized controlled trial (RCT) is to investigate the effects of Pycnogenol® versus placebo on self-reported health status (primary outcome) in people with PCC.

Secondary objectives are to assess the efficacy of Pycnogenol® versus placebo on PCC-related symptoms (e.g., fatigue, post-exertional malaise, dyspnea, cognitive function), health-related quality of life, symptoms of depression and anxiety, functional exercise capacity, physical activity, and biomarkers for inflammation, oxidative stress, coagulation, and endothelial function.

### Trial design {8}

This is a 12-week, single-center, placebo-controlled, quadruple-blind, parallel design superiority trial investigating effects of a daily dose of 200 mg Pycnogenol® versus a placebo. Randomization (1:1 allocation ratio) will be stratified for duration of PCC-related symptoms (i.e., ≤ 6 months vs. > 6 months) and presence of symptomatic chronic conditions.

## Methods: participants, interventions and outcomes

### Study setting {9}

This single-center study will be caried out at the Epidemiology, Biostatistics and Prevention Institute (EBPI) at the University of Zurich, Switzerland.

### Eligibility criteria {10}

#### Inclusion criteria

Age 18 years and olderSARS-CoV-2 infection confirmed by positive polymerase chain reaction (PCR) or rapid antigen test for professional use and/or physician confirmed diagnosis of PCCPCC (World Health Organization Definition [26]), i.e., ≥ 3 months after SARS-CoV-2 infection and ongoing or recurring symptoms for at least 2 months that cannot be explained by alternative diagnosisAt least one of the following symptoms must be present at screening: fatigue, cognitive impairment (“brain fog”), dyspnea, post-exertional malaiseSigned informed consentSufficient language and cognitive skillsAbility to participate in study visits at the study center or at home. Home visits are only possible if the travel distance by car is no longer than 90 min (one way) from the study center at the University of ZurichNo foreseeable change in medication

#### Exclusion criteria

Severe comorbidities such as liver or renal failure, advanced chronic obstructive pulmonary disease or pulmonary fibrosis requiring > 5 L oxygen/min at rest, active malignancy, advanced heart failure, and cardio-vascular events within the previous 24 weeksAcute respiratory or other infectionsClinical diagnosis of psychiatric disease that is untreated and/or unstableCOVID-19 vaccination less than 4 weeks prior to the baseline visit or during study participationKnown intolerance to Pycnogenol®Regular intake of Pycnogenol®Being enrolled in another interventional study that may interfere with the current study

### Who will take informed consent? {26a}

Prior to screening, potential participants are provided with information about the study including its nature, purpose, expected duration, and potential risks and benefits. The principal investigator (PI), or their formally trained designees, explain these details to each potential participant. To ensure that participants have sufficient time to consider their participation, they are given at least 24 h between the first contact and the screening visit. Before any investigation takes place, the participant’s formal consent is obtained using the informed consent form. Participants are required to read, understand, and voluntarily agree to the participation in the study before signing and dating the informed consent form. They are given a copy of their signed document for their records.

### Additional consent provisions for collection and use of participant data and biological specimens {26b}

An additional consent form for further use of data and biological material is given to the participants. The additional consent is not compulsory for participation in the study.

## Interventions

### Explanation for the choice of comparators {6b}

We choose a patient-reported outcome as primary endpoint in this study (EQ-VAS) [27, 28]. To differentiate the potential effects of Pycnogenol® from the placebo effect, this study utilizes a placebo that shares identical physical characteristics and dosing regimen with the verum. Using a placebo is ethically justified, as there is no approved treatment for PCC, and no treatment of proved effectiveness will be withheld. Additionally, participants are not required to discontinue any PCC-related treatment or medication prior to enrolment into the study, except regular intake of Pycnogenol®.

### Intervention description {11a}

Table 1 provides an overview of study procedures including interventions. Following assessment of inclusion and exclusion criteria, eligible subjects are randomly allocated to the verum or placebo group.

**Table 1 Tab1:**
[figure not shown]
Overview of enrolment, assessments and outcome measures according to Standard Protocol Items: Recommendations for Interventional Trials (SPIRIT)

*Abbreviations*: *CRQ*, Chronic Respiratory Questionnaire; *EQ-5D-5L*, EuroQol Questionnaire (5 levels); *EQ-VAS*, EuroQol Visual Analogue Scale; *FACIT-Fatigue*, Functional Assessment of Chronic Illness Therapy—Fatigue Scale; *HADS*, Hospital, Anxiety and Depression Scale; *MoCA*, Montreal Cognitive Assessment Test

^*^Primary outcome: The EQ-Visual Analogue Scale is assessed daily over 7 consecutive days prior to the baseline visit (V2) and follow-up visit 2 (V4)

^**^Blood biomarkers of inflammation, coagulation and platelet function, oxidative stress, and endothelial function

^***^Study visits can potentially impose a burden on participants. At each visit, starting with the baseline visit (V2), participants are asked whether they experienced a worsening of their PCC-related symptoms within 3 days after the last study visit

^****^Upon completion of the study, participants receive a link to an online survey to request feedback regarding the study organization

Participants in the intervention group receive 200 mg Pycnogenol® per day for 12 weeks, with two capsules containing each 50 mg in the morning and two capsules in the evening. Pycnogenol® is a proprietary French maritime pine bark extract (Pinus pinaster subsp., atlantica, Pinaceae) produced by Horphag Research, Geneva, Switzerland. Pycnogenol® is standardized to contain 70 ± 5% procyanidins in compliance with the United States Pharmacopeia. Its compounds and gut metabolites are known among other actions for their antioxidant properties, anti-inflammatory activities, and stimulation of nitric oxide production in vascular endothelial cells [22].

Participants in the control group receive a placebo. The placebo capsules are manufactured in the same facility and have the same physical appearance, consistency, and weight as the verum. Like the participants in the verum group, participants in the control group take two capsules twice daily with or right after a meal.

### Criteria for discontinuing or modifying allocated interventions {11b}

In general, Pycnogenol® is well tolerated [20, 21, 29]. In this study, Pycnogenol® is supplied at a dose of 200 mg per day, with two capsules containing 50 mg in the morning and two capsules in the evening taken together or right after a meal to avoid potential gastrointestinal discomfort. Gastrointestinal discomfort is the most frequently reported treatment-related side effect in previous clinical trials [29]. Further reported treatment-related adverse events are dizziness, headache, and nausea [29]. All side effects, possibly related to the study product, will be recorded as adverse events. Adjustments in study product dosage or intake are not planned.

Upon withdrawal or exclusion, early termination will be recorded in the database, and the participant will be invited for a termination visit. If the participant is not able or willing to participate in a termination visit, a phone call will be offered instead. Moreover, we will ask the participant if they are willing to complete the study specific questionnaires to keep missing data to a minimum. The participant will be asked to return leftover study products to the study center.

### Strategies to improve adherence to interventions {11c}

To enhance the validity of our data and adherence to study products, we planned a short study visit six weeks and two phone calls two respectively 9 weeks after randomization (Fig. 1) to stay in close contact with study participants. During the phone calls, the importance of adhering to the study products and monitoring symptoms in the diary is discussed. Study products returned at the follow-up visits (V3, V4, Fig. 1) are counted and recorded in the database. In addition to the intention-to-treat analysis (primary analysis), we plan a per protocol analysis based on adherence to study products and investigate its potential impact on primary and secondary outcomes.

**Fig. 1 Fig1:**
[figure not shown]
Participant timeline

### Relevant concomitant care permitted or prohibited during the trial {11d}

Concomitant medication including herbal medications or supplements is principally allowed. Investigators instruct participants to keep their therapy regimen unchanged during the study period. This also applies for concomitant non-pharmaceutical PCC-related therapies. Participants are instructed not to start any new therapy, new preventive measures such as COVID-19 vaccinations, or intervention during the trial that may interfere with study outcomes. Those who plan to get vaccinated against SARS-CoV-2 will get the opportunity to get vaccinated at our center prior to the baseline visit.

### Provisions for post-trial care {30}

Participants terminating the study (either regularly or prematurely) with reported ongoing serious adverse events (SAE) or any ongoing adverse events regarding laboratory values or vital signs being beyond the alert limit will be asked to return for a follow-up investigation. This visit will take place up to 30 days after termination of the treatment period.

### Outcomes {12}

Table 1 provides an overview of assessments including primary and secondary outcomes.

#### Primary outcome

The primary outcome is self-reported health status assessed with the EQ-VAS, also known as the “Feeling Thermometer” [27, 28]. The EQ-VAS is numbered from 0 to 100 with 0 representing the “worst imaginable health” and 100 representing the “best imaginable health.” The scale is frequently used in people with chronic respiratory conditions [30–32] and has a well-established minimal important difference (MID) of 5–8 units [31]. In our trial, EQ-VAS is assessed daily over seven consecutive days prior to the baseline visit (V2) and again prior to the last study visit (V4). Mean EQ-VAS scores (i.e., pre- and post-intervention) will be computed, including at least 4 days. Post-intervention, EQ-VAS scores will be compared between the intervention and placebo groups and adjusted for baseline values. In addition, self-reported health status is assessed at screening (V1) visit. These data will be used for descriptive purposes. A minimal important difference (MID) of 8 units will be used for interpretation of the magnitude and clinical relevance of between-group differences in post-intervention EQ-VAS values [31].

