*Health-related quality of life* is assessed with the EuroQol Questionnaire (EQ-5D-5L) questionnaire [27, 28]. The questionnaire includes five dimensions scored on five levels of severity. The Dutch value set will be used to calculate EQ-5D-5L index scores.

*Functional exercise capacity* is assessed with the 30-s sit-to-stand (STS) test [52–54]. A familiarization test is done at the screening visit (V1). Heart rate, oxygen saturation, and ratings of perceived exertion and dyspnea are recorded before and after the exercise test. A between-group difference of ≥ 2 repetitions post-intervention will be considered clinically relevant [53].

*Physical activity* is measured with a triaxial accelerometer (ActiGraph wGT3X-BT, Pensacola, FL, USA) worn around the hip for 8 consecutive days before baseline (V2) and study end (V4). Data will be used for the analysis if at least 4 days (including a weekend day) of measurements with a minimum of 10 h wear time per day are recorded. Physical activity will be expressed as daily step count and time spent in different intensity domains using validated cut-offs [55–57].

*Biomarkers of endothelial health* include soluble thrombomodulin, von Willebrand Factor antigen, syndecan-1, and sVCAM-1 [58–61] and are measured using commercially available enzyme-linked immunosorbent (ELISA) or Luminex (bead-based immunoassay) assays following the manufacturers instruction.

*Biomarkers of inflammation* include C-reactive protein (CRP), interleukin-6 (IL-6), and leukocyte levels [60, 62]. Blood levels of CRP- and IL-6, as well as leucocyte numbers as part of the hemogram, will be determined for each participant.

*Biomarkers of coagulation and platelet function* include soluble CD40 ligand (sCD40L) and plasma soluble P-selectin (sP-selectin) [58, 63–66] and will be measured using commercially available ELISA or Luminex assays following the manufacturers instruction. In addition, D-dimers, international normalized ratio (INR), activated partial thromboplastin time (aPTT), and platelet concentration as part of the hemogram will be assessed.

*Biomarker of oxidative stress* will be the total antioxidant capacity (TAC) of blood plasma using the fluorescence recovery after photobleaching (FRAP) method.

*Biomarkers of kidney and liver function* include serum creatinine levels to assess estimated glomerular filtration rate (eGFR), aspartate aminotransferase (ASAT), alanine aminotransferase (ALAT), and gamma-glutamyltransferase (γ-GT).

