### Safety outcomes

At each study visit (Table 1), vital signs (heart rate, oxygen saturation, blood pressure, body temperature) are measured. Blood pressure is measured in duplicate after resting for 5 min in sitting position (legs uncrossed) with a portable blood pressure monitor (Omron M3 Comfort). The average blood pressure value will be recorded and used for the descriptive analysis. Heart rate and oxygen saturation are measured in sitting position with a portable pulse oximeter (Beurer PO 80).

At the screening visit (V1), a 12-channel resting ECG (ELI™ 280, Hechingen, Germany) is performed with the participant in supine position (after at least 5 min rest) to screen for unstable cardiac disease. Furthermore, a blood sample is drawn to screen for other underlying causes for symptoms similar as those seen in individuals with PCC. The tests include blood count, ferritin, CRP, vitamin B12 levels, and thyroid-stimulating hormone (TSH) as well as kidney function (eGFR) and liver enzyme activity (ALAT, ASAT, γ-GT). Clinically relevant abnormal diagnostic laboratory parameters will be passed on to the participants so that necessary measures can be taken such as further diagnostics or treatment delivered through the participant’s attending physician.

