### Sample size {14}

Sample size calculations were based on data from a population-based prospective cohort study (Zurich SARS-CoV-2 Cohort) [3]. In this cohort (*n* = 1543), 208 (13.5%) study participants reported at least one symptom 6 months after the polymerase chain reaction (PCR) diagnosed SARS-CoV-2 infection [3]. The mean (SD) health status assessed with the EQ-VAS was 73.4 ± 16.5 on a 0–100 scale. Using the mean ± SD EQ-VAS data from this cohort and considering the MID of the EQ-VAS of 8 units [31] as reference, with 80% power, the estimated sample size is 136 subjects (i.e., 68 per group). This sample size allows us to detect a difference of 8 units in the EQ-VAS between the verum and placebo groups at 12 weeks. Assuming a drop-out rate of 10%, we aim to include a total of 150 subjects.

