## Statistical methods

### Statistical methods for primary and secondary outcomes {20a}

#### Primary outcome

The primary analysis will be done following the intention-to-treat (ITT) principle. All randomized participants having received at least one dose of Pycnogenol® will be included in this analysis. We will use multivariable linear regression models to compare EQ-VAS values at 12 weeks adjusted for baseline values and stratification factors, i.e., PCC duration (≤ 6 months versus > 6 months) and presence of any chronic disease(s).

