We have undertaken all efforts to design a methodologically robust trial, including blinding of study participants and the entire study team (investigators, sponsor, outcome assessors, data analyst) to reduce bias. Computer-based randomization and proper concealment of random allocation minimizes confounding and selection bias. We use validated instruments and integrated core outcome measures for studying the efficacy of Pycnogenol® versus placebo on PCC-related sequelae [72]. The primary endpoint was established with people with lived experience, and they confirmed that the EQ-VAS captures their daily symptom burden well. Due to the episodic nature of PCC-related symptoms and their impact on daily life, we assess health status (EQ-VAS) daily over 7 days at baseline and post intervention to be able to best capture those fluctuations.

The clinical diagnosis of PCC is complex and challenging [73]. Not all individuals enrolled in this study will have a physician diagnosis of PCC, which may introduce some uncertainty. However, we request confirmation of a SARS-CoV-2 infection by a positive PCR or rapid antigen test for professional use or a written medical report including a physician diagnosis of PCC. Additionally, we evaluate the plausibility of PCC-related symptoms by self-reported symptoms, symptom duration and start of persisting symptoms prior to inclusion into the study.

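### The screening EQ-VAS is kept for description only; entering it as a second pre-randomisation covariate would add a little precision at almost no cost

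*Protocol article*

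**What the plan says.** Under Outcomes, Primary outcome, the baseline EQ-VAS is the mean of daily ratings over the seven days before V2, with at least four days required. The screening rating has a separate role: "In addition, self-reported health status is assessed at screening (V1) visit. These data will be used for descriptive purposes". Under Statistical methods, Primary outcome, the regression will "compare EQ-VAS values at 12 weeks adjusted for baseline values and stratification factors". The secondary models take the same form, and Secondary outcomes ties their baseline to V2.

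V1 also yields earlier values of some secondary endpoints. On the screening blood sample, Safety outcomes states: "The tests include blood count, ferritin, CRP, vitamin B12 levels, and thyroid-stimulating hormone (TSH) as well as kidney function (eGFR) and liver enzyme activity". CRP, leukocytes, platelets, eGFR, ASAT, ALAT and gamma-GT all reappear in the list of secondary biomarkers. A practice sit-to-stand test is also done at V1. No section enters any of these V1 values in a model.

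**The concern.** The Discussion gives the reason for rating health status over a week: "Due to the episodic nature of PCC-related symptoms and their impact on daily life". Averaging seven days within one week removes most day-to-day noise but leaves any swing that lasts the whole week. A rating from a different week can therefore carry information about a person's usual level that the V2 mean lacks. Because it precedes randomisation, adjusting for it cannot bias the treatment comparison. At stake is some width of the confidence interval for the primary result and for a limited set of secondary ones. The data are already collected, and the plan states what they are for, so this is a choice that can be reviewed and not a detail left to the analysis plan.

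**Working it through.** **1. The plan's own figure.** Inputs from Sample size: difference 8, SD 16.5, power 80%. Alpha is not stated; 0.05 two-sided is assumed. The normal formula gives 2 × (1.960 + 0.842)² × 16.5² / 8² = 66.8, so 67 per arm. The noncentral t gives power 0.796 at 67 and 0.801 at 68 per arm. This matches "with 80% power, the estimated sample size is 136 subjects". The SD is unadjusted, so the 136 takes no credit for baseline adjustment. With the planned V2 adjustment, power at 68 per arm is already about 0.87, 0.90, 0.94 or 0.98 if the V2–V4 correlation is 0.4, 0.5, 0.6 or 0.7.

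**2. Model for adding V1 (all inputs assumed).** Split the variance of one rating into person T, week S and day E. V1 is taken as one rating three weeks before V2; V4 is 12 weeks after V2. Week effects correlate as ρ to the power of the gap in weeks.

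- Var(V1) = T + S + E; Var(V2) = Var(V4) = T + S + E/7
- Cov over a gap of g weeks = T + S·ρ^g
- With r = corr(V2,V4), s = corr(V1,V4), q = corr(V1,V2): R² with V2 alone = r²; R² with both = (r² + s² − 2rsq)/(1 − q²)

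Example with T/S/E = 0.5/0.3/0.2 and independent weeks: Var(V2) = 0.829, r = 0.5/0.829 = 0.603, s = q = 0.5/√0.829 = 0.549. R² rises from 0.364 to 0.432, and residual variance falls by 1 − 0.568/0.636 = 10.7%.

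The table gives the same example under four values of ρ. The grid column covers T 40–70%, S 10–40% and E 20–30%. Half-width is that of the 95% interval, 1.978 × 16.5 × √(1 − R²) × √(2/68). Power is for 8 units with 68 per arm.

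| ρ per week | R², V2 → V2+V1 | Fall in residual variance | Over grid | Half-width | Power |
|---|---|---|---|---|---|
| 0 | 0.364 → 0.432 | 10.7% | 8.2–12.6% | 4.46 → 4.22 | 0.941 → 0.961 |
| 0.5 | 0.364 → 0.421 | 9.0% | 6.9–10.7% | 4.46 → 4.26 | 0.941 → 0.958 |
| 0.8 | 0.395 → 0.420 | 4.1% | 3.1–5.5% | 4.35 → 4.26 | 0.950 → 0.958 |
| 0.9 | 0.498 → 0.508 | 1.9% | 1.4–3.2% | 3.97 → 3.93 | 0.977 → 0.979 |

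**3. Cross-check with correlations set directly.** r/s/q = 0.5/0.4/0.6 gives R² 0.250 → 0.266, a fall of 2.1%; 0.6/0.5/0.6 gives 0.360 → 0.391, a fall of 4.8%. Larger gains (17% at 0.7/0.7/0.7) need one V1 rating to predict week 12 as well as the seven-day mean does, which I would not assume.

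**4. Cost.** The planned model has five parameters, leaving 131 residual degrees of freedom on 136. One more covariate inflates the variance by about 1/130 = 0.8%.

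**5. Markers with one value per visit.** With the same correlation r between any two visits, R² goes from r² to 2r²/(1 + r):

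- r = 0.4: 0.160 → 0.229, fall 8.2%
- r = 0.6: 0.360 → 0.450, fall 14.1%
- r = 0.8: 0.640 → 0.711, fall 19.8%

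If correlation decays with time, the gain shrinks. r/s/q = 0.6/0.58/0.8 gives 4.3%; 0.5/0.45/0.8 gives 0.9%, which the lost degree of freedom almost cancels.

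**The case against.** The strongest reply is that the plan contains no error. The primary model is a sound baseline-adjusted regression on a well-averaged baseline, and it also includes both stratification factors; a reader who took it to adjust for nothing but the V2 score would be mistaken. The sample size already has slack. Even in the most favourable column of the example, the half-width moves by about a quarter of a unit against a minimal important difference of 8. The correlations and the three-week gap are assumptions, since the timeline figure and Table 1 are not shown, and the word episodic says nothing about week-to-week variance. Changing the primary model of an approved protocol during recruitment is also not a trivial act. All of this stands, and it limits the importance of the point.

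A reader might also infer that the secondary endpoints gain broadly. The text does not support that. FACIT-Fatigue, CRQ dyspnea, MoCA, HADS, accelerometry and the in-house biomarkers are described only at V2 and V4. The kidney and liver markers that do have V1 values are missing from the abstract's list of secondary endpoints and from the objectives. The V1 sit-to-stand is a practice trial. A practice shift common to everyone would be absorbed by the intercept, but learning that differs between people would weaken V1 as a predictor.

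None of this shows a material downside to using the V1 values. The worst case under the assumptions tried is a gain close to zero.

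**Conclusion.** The point holds as a low-severity efficiency suggestion. A valid pre-randomisation measurement is collected and then kept out of the model. The residual variance of the primary outcome would fall by 1.4% to 12.6% under the assumed variance splits, less about 0.8% for the extra covariate. The upper end needs week-level swings to be independent; with carry-over of 0.8 to 0.9 per week the fall is 1.4% to 5.5%. For single-value markers it is about 1% to 20%, with the upper end resting on correlations that do not decay over time. Confidence that the change is valid is high; confidence in the size of the gain is low, because the documents give no correlation.

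A reader might infer that leaving V1 out biases the comparison or leaves the trial short of power. It does neither: both models are unbiased under randomisation, and the stated 136 reaches 80% power for 8 units before any adjustment.

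**What to change.** In Outcomes, Primary outcome, give the V1 EQ-VAS the role of a further covariate in the primary model. In Statistical methods, define baseline adjustment as the V2 value plus the V1 value wherever V1 exists: EQ-VAS, CRP, leukocytes, platelets, eGFR, ASAT, ALAT and gamma-GT, and, with less certainty, sit-to-stand. Fill a missing V1 covariate with the mean of all participants' pre-randomisation values, pooled over arms, so that nobody is lost. Carry the same covariates into the multiple-imputation model for missing V4 data.

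Fix the change in writing before unblinding, as a documented amendment and not as a later deviation; the section on non-adherence and missing data restricts substantial deviations to unforeseen circumstances. The cost is a short wording change, that amendment, one degree of freedom per affected model, and covariate sets that differ between secondary outcomes. It needs no new data or visits.
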